**Figure 2 Fig2:**
[figure not shown]
**Study flow.**

### Clinical setting: cardiac rehabilitation in the Netherlands

The study will take place in Dutch CR clinics that already work with an EPR with CDS at the point of care. CR is a therapy provided by multidisciplinary care teams to support heart patients recover from a cardiac incident or intervention, and aims to improve their physical and psychological condition [27-31]. CR is recommended for all patients who have been hospitalized for an acute coronary syndrome (ACS) and for those who have undergone coronary revascularization (coronary artery bypass graft surgery [CABG] or percutaneous coronary interventions [PCI]) or valvular surgery [32,33]. Recent studies show that CR is also beneficial for patients with other chronic cardiovascular conditions such as stable angina pectoris (AP) and chronic heart failure (CHF) and for subjects with a high risk for developing cardiovascular disease [34]. A recent meta-analysis shows consistent evidence of the effectiveness of exercise-based and multimodal (e.g., psychosocial and stress management) CR interventions with regard to mortality and prevention of future cardiac events (relative-risk reduction 21–47%) [35]. CR teams usually include cardiologists, physical therapists, nurses, psychologists, dieticians, social workers, and rehabilitation physicians. It has proven to be cost-effective in different economic evaluations conducted in North America and Europe [29]. However, in many Western countries, CR services are under-utilized and poorly standardized and do not follow the available scientific evidence [36]. A recent study in the Netherlands shows that only a minority of patients eligible for CR actually receive it [37]. The CR uptake rate was 28.5% among patients with an ACS and/or intervention. From these, patients who underwent CABG or valve surgery had the highest uptake rate (58.7%) and patients with an ACS without an intervention had the lowest uptake rate (9.8%) [37].

### Context: the use of CDS in participating CR clinics

All participating CR clinics use an EPR with CDS based on the most recent version of the CR guidelines [26]. The CDS provides advice on a patient-tailored rehabilitation program based on the needs assessment procedure. This procedure requires gathering 80 to 130 data items concerning the patient’s health status and rehabilitation needs. A clinical algorithm describing a branching logic to assess the data is part of the guidelines [38]. The rehabilitation program can contain four possible group-based therapies: exercise training (optimize exercise capacity with physical restrictions); education therapy (about consequences of the patient’s disease); lifestyle change therapy (risk-related behavioral adjustment); relaxation and stress management training (learning to manage tension in daily practice); and if needed, different forms of individual therapy (e.g., by psychologists). During the needs assessment procedure, the CDS advice can immediately be discussed with the patient to set the final rehabilitation program.

### Intervention

We will carry out a multifaceted guideline implementation intervention that consists of two elements: (i) quarterly feedback on quality indicators for CR, provided as part of a web-based QI system and (ii) educational outreach visits using the same system to set up a QI plan together with a local QI team. Table 2 gives an overview of the complete intervention for both study arms.i.)Feedback. Each 3 months, all participating clinics will receive feedback on a set of quality indicators for CR [24], based on data that are recorded by the CDS system. Feedback reports will be presented within the web-based QI system called CARDSS Online, which was specifically developed for this study [39]. Within this system, clinics can monitor their performance on the quality indicators listed in Table 3. Figure 3 shows a screenshot from the feedback report page in CARDSS Online. After clicking on an indicator button, a pop-up screen opens with detailed information about data underlying the calculation, national averages for comparison, and benchmark values. Feedback will be attuned to the research arm concerned: clinics allocated in arm A will receive feedback on quality indicators referring to psychosocial domain; clinics allocated in arm B will receive feedback on indicators referring to the physical domain. Both arms will receive feedback on indicators referring to general processes and structures (see Table 3).To assist the QI teams with selecting the quality indicators requiring improvement, a colored icon next to each indicator score indicates whether the performance is acceptable (green checkmark), borderline (orange checkmark), or poor (red exclamation mark). In addition, results will be compared to statistics from the same clinic during earlier periods to quantify change. When a clinic’s average for a given indicator is poor or differs (both in positive and negative sense) from previous results, this will be discussed during the outreach visits. Icon colors are automatically determined by the CARDSS Online system, using predefined rules (see Appendix I).ii.)Outreach visits*.* Feedback reports will be received by all participating clinics on a 3-month basis and followed by outreach visits to support interpretation of the report and to draft a QI plan. This approach was chosen to match the conclusion from the Cochrane review that the feedback may be more effective when it includes both an action plan and explicit goals [17]. During development of the QI plan content, additionally, the goal-setting theory, stating that feedback and well-specified goals are indeed a successful combination, was used. The theory emphasizes that people tend to be more committed to attaining a certain goal if they are involved in setting it, if (the outcome of) goal attainment is seen as important, and if people believe they are capable of accomplishing it [40]. To this end, each clinic needs to set up a local QI team with the responsibility to define, implement, and monitor a QI plan including concrete QI goals based on self-identified issues in the feedback reports.QI team: Setting up a QI team implies the allocation of at least two CR team members for an average of 3 h per month (anyhow, the nurse acting as rehabilitation coordinator and one person from another discipline) and two members for an average of 1 h per month (a cardiologist and a representative from the management) during the study.QI plan: The QI team can use CARDSS Online to grade indicators that the team aims to improve based on importance (five categories), feasibility (five categories), and expected time needed (three categories). CARDSS Online then ranks the indicators based on assigned ratings, and the team can select indicators for final inclusion in the QI plan. In principle, all quality indicators can be selected for improvement, but teams are encouraged to focus on a small subset of three to four indicators during each 3-month cycle. For each quality indicator included in the QI plan, users can specify the problem, presumed causes, improvement goal, and concrete actions on how to reach that goal. CARDDS Online does not provide tools, other than documentation, for systematic problem analysis or suggestions for improvement actions. For each action, the names of responsible team members and a deadline for achievement has to be entered.

**Table 2 Tab3:** **Elements of the multifaceted guideline implementation intervention for both study arms per cardiac rehabilitation therapy**

**Study arm**	**CR therapy**	**Elements**	**Description of the elements**
A	Exercise training	CDS	Computerized decision support system at the point of care based on the most recent guidelines for CR
	Relaxation and stress management training	CDS	
	Education therapy	CDS	
		Feedback	Quarterly feedback reports on quality indicators for CR for arm A and B (see Table 3), monitoring of own performance over time, comprehensive benchmarking CR clinic’s performance to the other participating clinics
		Educational outreach visits	On site educational outreach visits after sending the feedback reports, supporting discussion of feedback results within a local QI team, supporting this team to define, implement and monitor a QI plan by means of a web-based QI system (CARDSS Online)
	Lifestyle change therapy (excluding physical activity)	CDS	
		Feedback	
		Educational outreach visits	
B	Exercise training and physical activity	CDS	
		Feedback	
	Relaxation and stress management training	CDS	
		Feedback	
		Educational outreach visits	
	Education therapy	CDS	
	Lifestyle change therapy	CDS

**Figure 3 Fig3:**
[figure not shown]
**Screenshot CARDSS Online (feedback report).**

Four to six weeks after the first outreach visit, a telephone call will take place with the chair of the local QI team to discuss and support resolution of possible problems that occur during the implementation of the QI plan. Three months after the first round of feedback, a new feedback report is composed and becomes available in the system. During, but also in between, outreach visits, local QI teams can access CARDSS Online to provide status updates on actions listed in the current QI plan.

During the study period of 1 year, all clinics will receive four feedback reports, four outreach visits, and (at least) one telephone call. All visits will be carried out by the same investigator ([name]) who has a health sciences background; she has been involved in the development of the CR quality indicator set [24] and has several years of experience with CR guideline implementation [41].

#### CARDSS online

The system was designed as a web-based application which can be consulted by all participating CR clinics. We designed the system to be primarily employed during educational outreach visits with the clinic’s QI teams. At the server side, CARDSS Online consists of a Microsoft SQL Server database and a Java web application. At the client side, clinics can use any web browser that is capable of rendering HTML and executing JavaScript. Development of the system and the architecture are described in more detail elsewhere [39].

### Participants

#### Inclusion criteria (clinic level)

All CR clinics that use an EPR for CR with CDS during the CR needs assessment procedure and that are willing to dispose their data for research and to set up a QI team are eligible to participate in the study. There are 91 CR clinics in the Netherlands, the majority affiliated with hospitals [42]. Twelve clinics are located in specialized rehabilitation centers [42], who have regional functions and can treat simple but especially more complex referred patients. Both types of clinic work according to the same guidelines and are eligible to participate in the study.

In the Netherlands, there are two commercial vendors of CDS systems for CR that can be used for data collection. Both systems have been validated for their advice being completely consistent with the guidelines. Also data collection in these systems is in line with the minimal dataset of our study. The minimal dataset is based on the set of 18 quality indicators for CR (see Table 3) and consists of (i) patient identification data (31 items), (ii) CR needs assessment data (80–130 items, see Table 4), (iii) data on selected rehabilitation goals and therapies (79 items), and (iv) CR evaluation data (105 items). Clinics that use one of the CDS systems automatically collect the right data items. The price of both systems depends on contract conditions, but amounts on average to €20,000 for purchase and to €4,000 per year for service, updates, and maintenance.

**Table 4 Tab4:** **Items which need to be measured during the needs assessment procedure according to recommendations in the Cardiac Rehabilitation Guidelines** [26,38]

**Domain**	**Item**	**Clinical algorithm cardiac rehabilitation 2012**
1. Physical functioning	Objective exercise capacity	Maximal symptom limited exercise tolerance test.
		For patients with heart failure: completed with a spiroergometry (VO2max) test [43].
	Subjective exercise capacity	MacNew Quality-of-Life questionnaire (27 questions) [44,45]
2. Psychological functioning	Emotional function	MacNew Quality-of-Life questionnaire (27 questions) [44,45]
	Anxiety and Depression	Option 1: Generalized Anxiety Disorder scale (GAD-7, 7 questions) [46] in combination with the Patient Health Questionnaire (PHQ-9, 9 questions) [47]
		Option 2: Beck Anxiety Inventory (BAI, 21 questions) [48] in combination with the Beck Depression Inventory (BDI, 21 questions) [49]
		Option 3: Hospital Anxiety and Depression Scale (HADS, 14 questions) [50]
3. Social functioning	Social function	MacNew Quality-of-Life questionnaire (27 questions) [44,45]
	Social support	Option 1: Multidimensional Perceived Social Support Scale (MPSSS, 12 questions) [51,52]
		Option 2: ENRICHD Social Support Inventory (ESSI, 7 questions) [53]
	Life Partner	Clinical interview (3 questions)
	Resumption of work	Clinical interview (10 to 18 questions)
4. Cardiovascular risk profile	Cardiovascular risk profile	Physical examination (obesity, blood pressure), blood testing (cholesterol and diabetes)
5. Lifestyle factors	Smoking status	Clinical interview (1 to 4 questions) and specific treatment advice
	Physical activity	Monitor ‘Physical activity and Health’ (4 questions) [54]
	Dietary habits	Individual screening by dietician (in case of hypertension, hypercholesterolemia, obesity, or diabetes)
	Alcohol consumption	Five Shot questionnaire (5 questions) [55,56]

#### Inclusion criteria (patient level)

All consecutive CR patients that undergo the needs assessment procedure in one of the participating clinics will be included in the study. Clinics that participate in the study agree to enter all data of these patients in their EPR.

#### Recruitment

To promote participation and avoid volunteer effects, all CR clinics that use an EPR with CDS will receive a written invitation and, when they agree, will be visited by a member of the CARDSS team. During this introduction, the study protocol is explained to all team members, including the manager and cardiologist. Furthermore, the study is announced at national meetings of professional CR associations and during the 2-yearly national CR conference (visited by more than 350 professionals). After agreement on participation, the responsible administrator of the CR department (often the manager or the executive board of the hospital) must sign a consent form to formalize the organization’s commitment.

### Outcome measures

As in most guideline implementation studies, the proposed intervention is targeted at health care providers and is therefore expected to have a direct effect on process outcomes and to have only indirect, long-term effects on patient outcomes. The primary outcome measure will therefore be concordance, at patient level, to national CR guidelines with respect to the needs assessment (concordance of clinical decisions with the guidelines, for four group-based therapies). We will measure whether patients are treated according to the recommendations of the guidelines (i.e., treating patients who should have been treated and not treating patients who should have been untreated).

Secondary outcome measures are changes in performance of participating clinics as measured by 18 quality indicators for CR (see Table 3) and changes in practice variation on these indicators. Table 1 describes how the indicator set was developed [24].

### Data collection and validation

During the trial, participating CR clinics will use one of the two available commercial EPR systems with CDS. Each month, participating clinics are requested to extract data from their EPR, and submit it to the CARDSS Online system. After submission, the data are checked for validity and imported to the CARDSS Online database.

To measure data quality and completeness, a data audit will be conducted in each participating clinic at the end of the trial. To do so, we will ask access to an independent, local data source (preferably a digital agenda listing appointments for all therapies offered to CR patients). First, we will use this data source to check if our registration of therapies is correct, i.e., whether these therapies were indeed attended by the patient. To this end, 20 patients randomly selected from our database will be looked up in the independent data source. Second, we will use this source to check if our database is complete, i.e., whether all data of CR patients treated at the clinic also exist in our database (no missing patients). Therefore, 20 patients randomly selected from the independent source will be looked up in our database.

When no independent data source is available, we will ask the clinic in question to interview ten randomly selected patients over the telephone about the therapies they have followed and to check if their answers match our database. Thereafter, we will ask the clinics if we can interview ten randomly selected patients during a therapy session to see if their data is present in our database and if the therapy programs match.

If two or more of the selected patients from the independent source cannot be found in our database or if discrepancies in therapeutic data exist in more than five records, we will consider all the data of the clinic in question to be unreliable and exclude that clinic from the analyses.

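### The completeness audit samples from a narrower group than the study population, so omitted patients who never had a therapy appointment cannot be found

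*Protocol article*

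**What the plan says.** All three elements are in the Methods of the protocol article.

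- **Population.** Under Inclusion criteria (patient level), the enrolment rule reads: "All consecutive CR patients that undergo the needs assessment procedure in one of the participating clinics will be included in the study". The same section adds: "Clinics that participate in the study agree to enter all data of these patients in their EPR". Membership depends on the assessment, not on whether therapy follows.
- **Primary outcome.** Under Outcome measures, concordance is judged for four group-based therapies and runs both ways: "treating patients who should have been treated and not treating patients who should have been untreated".
- **Audit.** Under Data collection and validation, the independent local source is "preferably a digital agenda listing appointments for all therapies offered to CR patients". The completeness check asks "whether all data of CR patients treated at the clinic also exist in our database (no missing patients"), and for this "20 patients randomly selected from the independent source will be looked up in our database". Where no such source exists, the investigators will "interview ten randomly selected patients during a therapy session to see if their data is present in our database". The exclusion rule begins "If two or more of the selected patients from the independent source cannot be found in our database"; a clinic that meets it is dropped from the analyses.

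**The concern.** The audit is the only check described for whether the database holds everyone it should. Its sampling frame is people with therapy appointments or people attending therapy. The database is supposed to hold everyone assessed. The gap between the two is the assessed patients who never had a therapy appointment. They count in the primary outcome: as non-concordant where therapy was recommended, as concordant where it was not.

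The clinics supply the data themselves each month. They cannot be blinded and are benchmarked on those data. If patients without therapy are recorded less completely, recorded concordance moves with no change in care, and the one planned safeguard cannot see it. The clinic would pass on completeness and stay in the analysis.

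**Working it through.** **Step 1. Who can be sampled.** The plan states no detection probability for the audit, so there is no figure to reproduce. Set side by side:

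| Audit element | Starts from | Can it reach an assessed patient with no therapy appointment who is not in the database? |
|---|---|---|
| Accuracy check, 20 patients | the study database | No, it starts from patients already recorded |
| Completeness check, 20 patients | preferably the therapy agenda; scope is treated patients | No |
| Fallback telephone interviews, ten patients | therapies followed, compared with the database | No, it checks recorded therapies |
| Fallback interviews, ten patients | a therapy session | No |

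No step starts from a list of intakes or needs assessments.

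**Step 2. Probability that the completeness rule is triggered.** Let q be the chance that a sampled patient is absent from the database. With 20 patients and a threshold of two,

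P(exclude) = 1 - (1-q)^20 - 20q(1-q)^19.

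If a clinic omits only patients without a therapy appointment, q = 0 in the agenda frame and P(exclude) = 0, whatever share is omitted and whatever the sample size. If the 20 came from a list of all assessed patients, q would equal the omitted share u:

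| u (assumed) | Therapy agenda | Intake list |
|---|---|---|
| 2% | 0% | 6% |
| 4% | 0% | 19% |
| 5% | 0% | 26% |
| 10% | 0% | 61% |
| 15% | 0% | 82% |
| 20% | 0% | 93% |

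For example, at 4%: 1 - 0.96^20 - 20 × 0.04 × 0.96^19 = 0.19.

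**Step 3. Effect on recorded concordance.** Let C be true concordance among all assessed patients and c the concordance of those omitted. Then

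recorded concordance = (C - u·c)/(1 - u).

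This exceeds C when c is below C and falls short of C when c is above it. The values of C are the reference levels under Sample size: exercise 92.6%, education 87.6%, relaxation 59.6%, lifestyle change 57.4%. The document gives neither u nor c, so both are assumed. For exercise with u = 5%:

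- c = 0%: 92.6/0.95 = 97.5%, a shift of +4.9 points
- c = 50%: (92.6 - 2.5)/0.95 = 94.8%, +2.2 points
- c = 100%: (92.6 - 5)/0.95 = 92.2%, -0.4 points

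Shift in points for all four therapies at u = 5%:

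| Therapy | c = 0% | c = 50% | c = 75% | c = 100% |
|---|---|---|---|---|
| Exercise | +4.9 | +2.2 | +0.9 | -0.4 |
| Education | +4.6 | +2.0 | +0.7 | -0.7 |
| Relaxation | +3.1 | +0.5 | -0.8 | -2.1 |
| Lifestyle change | +3.0 | +0.4 | -0.9 | -2.2 |

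At u = 2% the exercise shifts for c = 0%, 50% and 100% are +1.9, +0.9 and -0.2. At u = 10%, relaxation shifts by +6.6, +1.1 and -4.5 and lifestyle change by +6.4, +0.8 and -4.7.

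**Step 4. From level to effect.** Under Statistical analysis the effect is the time × arm interaction. A shift in level that is constant over time, or changes alike in both arms, largely drops out of it. Only omission that changes differently between arms enters the estimate.

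**The case against.** The case on the other side is substantial, and much of it stands.

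- **Direction.** A reader might infer that a clinic omitting these patients would show inflated concordance. The document does not support that as a general statement: correctly untreated patients count as concordant, and leaving them out lowers the rate. Upward bias is the likelier direction for exercise and education, where the reference levels are high. For relaxation and lifestyle change the sign can easily reverse.
- **Main source.** A reader might also suppose that patients with no therapy at all are the chief source of under-treatment. Nothing says so. Concordance covers four therapies, and a patient given exercise training but not a recommended education programme is under-treated yet appears in the agenda.
- **Comparison with the target effect.** It is tempting to set a shift of nearly 5 points beside the 5-point increase sought for exercise. That puts a level shift under an extreme assumption against a difference in change between arms. Both arms receive quarterly feedback, benchmarking and visits, so the incentive is broadly similar. Omitting a whole patient also removes that patient from both domains, not only the one targeted in that arm.
- **Workflow.** Under Context, decision-support advice is generated from data gathered during the needs assessment. Entry would therefore normally come before it is known whether therapy follows. Selective omission is possible but is not the described routine.
- **Frame.** The agenda is a preference rather than a requirement, and it lists appointments, so patients booked who never attended are in it.

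The mismatch itself survives. Whatever source is used, the check is worded for treated patients, the fallback takes place at a therapy session, and nothing requires a source that lists intakes. Nor is this a detail left to a fuller document: the article itself fixes the preferred source, scope, sample sizes and exclusion rule.

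**Conclusion.** The point holds as a mismatch between audit frame and study population. With a therapy agenda or therapy session as the source, omitted patients who never had a therapy appointment are detected with probability zero, and a conclusion that no patients are missing does not follow. This part rests on the text alone.

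The consequence for concordance is conditional. Recorded levels are biased upward if the omitted patients should have been treated and downward if they were rightly left untreated. For exercise at 5% omitted, the range is +4.9 to -0.4 points. These sizes rest on assumed omission rates and assumed concordance among the omitted; the document gives neither.

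A biased treatment effect should not be inferred. It would require omission to change over the year differently in the two arms, and the document does not show that. The finding is a gap in a safeguard that can be narrowed cheaply, not evidence that the trial result would be wrong.

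**What to change.** Draw the 20 completeness-check patients from a clinic list of intake or needs-assessment appointments, or of CR referrals, covering the trial year. The list should be independent of the study EPR and include patients whether or not therapy followed. If referrals are used, first restrict the list to patients who were actually assessed, since only they belong in the database. Draw the fallback sample from the same kind of list instead of from a therapy session. Reword the check so that it covers all assessed patients. Keep the therapy agenda for the accuracy check, where it is the right source.

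The number of records stays the same. The cost is that some clinics must produce a different list, and the document does not establish that an independent one exists everywhere; where it does not, the report should say so.

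The change improves detection without making it strong. With 20 patients and the two-missing rule, about 81% of clinics omitting 4% would still pass (100% - 19%), and about 39% of those omitting 10% (100% - 61%). The audit should therefore be reported as the number found out of the number sampled, per clinic and by arm, and not as showing that no patients are missing.

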### Randomization and allocation

We will randomly allocate CR clinics (clusters) to one of the both study arms, stratified by the number of patients per month entering the CR program: small (up to 30 patients) versus large (30 patients or more). Allocation is based on randomization with variable block size (two or four), performed with dedicated computer software written in the statistical programming language R (version 2.13.1). To conceal allocation, the software is used to generate a list of unique codes for both strata, where each code corresponds to an allocation (study arm A or B).

Three researchers will be involved in the allocation procedure. When a clinic is willing to participate, the first researcher ([name]) will determine its stratum and communicate that to a second researcher ([name]) (without naming the clinic involved). The second researcher will look up the next unique code on the list for this stratum and pass that code to a third researcher who can determine the study arm, based on the given code. Using this procedure, both the second and third researchers are fully blinded for the allocation of clinics to the study arms during the procedure. The first researcher is not blinded but can however during this procedure not influence the allocation. Due to the characteristics of the intervention, it will not be possible to blind participants or the investigators providing the intervention.

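### In the fallback audit, one of the two therapy-data checks (ten of 20 patients) is both carried out and judged by the clinic being audited

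*Protocol article*

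**What the plan says.** Under Data collection and validation, the protocol article plans an audit of every clinic at the end of the trial. For the standard audit, "we will ask access to an independent, local data source", preferably an appointment agenda. Two look-ups follow. For correctness of the therapy registration, "20 patients randomly selected from our database will be looked up in the independent data source". For completeness of the database, "20 patients randomly selected from the independent source will be looked up in our database".

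Where no such source exists, two steps replace these look-ups. For the first, "we will ask the clinic in question to interview ten randomly selected patients over the telephone about the therapies they have followed". The clinic's other task in this step is worded "and to check if their answers match our database". For the second, "Thereafter, we will ask the clinics if we can interview ten randomly selected patients during a therapy session"; this step covers both presence in the database and agreement of the therapy programme.

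A clinic is dropped from the analyses entirely if two or more patients from the independent source cannot be found, or if therapy discrepancies occur in more than five records. These limits are not restated for the fallback.

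Under Randomization and allocation, the article says that "it will not be possible to blind participants or the investigators providing the intervention".

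**The concern.** The standard audit rests on a source outside the clinic's own registration. The first fallback step gives that up: the clinic that entered the therapy records telephones the patients and also decides whether their answers agree with those records. The text describes no verification of the calls or of the matching.

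This matters for two reasons. First, the audited data are the therapies patients received, and the primary outcome (Outcome measures) is whether patients were treated as the guidelines recommend. Second, the audit result decides whether a whole cluster stays in the analysis. Under Sample size the trial aims for at least 19 clinics, so each cluster kept or dropped counts. If doubtful answers are read in favour of the record, a clinic with poor therapy registration could stay in the analysis as an audited clinic.

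**Working it through.** **1. The two fallback steps, set against the standard checks.**

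| | Correctness of therapy records | Completeness of the database |
|---|---|---|
| Standard audit | 20 patients, database to independent source | 20 patients, independent source to database |
| Fallback | 10 patients by telephone; clinic interviews and clinic judges | 10 patients at a therapy session; study team interviews, also checks the therapy programme |

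The article does not say from what list the ten telephone patients are drawn. I read this step as the counterpart of the first standard check, so starting from database records. The team's step starts from attendance and looks back to the database. It cannot draw a patient who is recorded as treated but never attended or has stopped, and that is the kind of error the first standard check is meant to find. The team's step also needs the clinic's consent and, at the end of the trial, reaches current patients only.

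**2. Inputs for the illustration.**

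- 10 clinic-judged and 10 team-judged patients; exclusion if more than five records are discrepant (Data collection and validation).
- Assumption: the limit applies to the 20 fallback records pooled. The article gives no denominator.
- Assumption: true discrepancy rate q, the same in both sets of ten. The article gives none.
- Assumption: the clinic reports a share s of its true mismatches, with s = 1, 0.5 or 0. The article gives none.

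There is no stated audit error rate in the article to reproduce.

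**3. Formula.** P(exclusion) = P(X + Y ≥ 6), with X ~ Binomial(10, s·q) for the clinic's ten and Y ~ Binomial(10, q) for the team's ten, independent.

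**4. Results, pooled reading.**

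| True rate q | s = 1 | s = 0.5 | s = 0 |
|---|---|---|---|
| 20% | 19.6% | 6.5% | 0.6% |
| 30% | 58.4% | 28.2% | 4.7% |
| 40% | 87.4% | 58.7% | 16.6% |
| 50% | 97.9% | 83.0% | 37.7% |
| 60% | 99.8% | 95.3% | 63.3% |

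The s = 1 column equals the standard 20-record check, Binomial(20, q). The s = 0 column is the team's ten alone, P(Y ≥ 6).

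**5. Sensitivity to the reading of the limit.** If more than five is applied to each set of ten separately, P(exclusion) = 1 − (1 − P(X ≥ 6))(1 − P(Y ≥ 6)).

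- q = 60%, s = 1: 1 − (1 − 0.6331)² = 86.5%.
- q = 60%, s = 0.5: 1 − (1 − 0.0473)(1 − 0.6331) = 65.0%.
- q = 30%, s = 1: 1 − (1 − 0.0473)² = 9.2%. With s = 0 it is 4.7%, so on this reading self-judgement can lower detection at that rate by at most 4.5 percentage points, because detection is already poor.

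**The case against.** The strongest reply is that the fallback does not consist of the clinic's calls alone. The very next sentence has the study team interview ten more patients and compare both database presence and therapy programme. Half of the therapy check is thus judged by the team, and the completeness check involves no judgement by the clinic. This stands, and it limits the point.

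A reader might infer that the whole check deciding a clinic's retention is a self-audit. Taking the clinic's ten calls alone at a true rate of 60%, detection would fall from 63% to 5% when half the mismatches are hidden. The text does not support that: with the team's ten included, the same case goes from 99.8% to 95.3% pooled, or from 86.5% to 65.0% if each ten is judged separately.

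A reader might also infer that fallback clinics have weaker records, or that knowing the arm biases the comparison. Neither is supported. Lacking a separate appointment source says nothing about the quality of the electronic record, which every participating clinic uses. Each clinic receives the intervention in one domain and serves as control in the other, the telephone step is the same in both arms, and no route to a bias favouring one arm is shown. Nor does the article describe a penalty that would give a clinic a motive to hide errors; favourable reading of doubtful answers is an assumption.

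Finally, it can be said that an article leaves audit detail to the full protocol. That holds for forms and staffing. Here, however, the article itself states who interviews and who matches.

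**Conclusion.** The point holds in a limited form. In clinics without an independent source, ten of the 20 audited patients are interviewed and judged by the audited clinic. The team's ten only partly make up for this, for the reasons in step 1 of the working.

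The size depends on assumed rates. On the pooled reading, half-reporting cuts the probability of excluding a clinic with 30% discrepant records from 58.4% to 28.2%. At 60% the loss is small (99.8% to 95.3%), because the team's ten then nearly suffice. These figures also assume that the clinic agrees to the team's interviews and that session attenders have the same error rate as the other patients; if not, the team's step protects less.

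The number of fallback clinics is not given and may be zero, so the effect on the trial as a whole cannot be stated. The likely harm is that some clinics with unreliable therapy data are retained. The change is worth making because it is nearly free and cannot be made once the audit has been done.

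**What to change.** Change the telephone step so that the study team draws the ten patients from the database, the clinic records each patient's answers on a form that shows no database entries, and the team alone compares the forms with the database. The team member who matches should not know the clinic's arm, and so should not be the investigator who carries out the outreach visits.

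In the same sentence, state whether the limit of more than five discrepant records applies to the 20 fallback patients together or to each ten.

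The cost is a little extra matching by the team already running the audit. The clinic makes the same ten calls as now, and the team needs no new access to patients. Calls by the team itself would also work, but could raise questions of access, since the article describes consent at the level of the organization only.
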